## Abstract

**Background:**

Screening for coronary artery disease (CAD) remains broadly performed in patients with type 2 diabetes (T2DM), although the lack of evidence. We conduct a real-world evidence (RWE) study to assess the risk of major clinical outcomes and economic impact of routine CAD screening in T2DM individuals at a very high cardiovascular risk.

**Methods:**

SCADIAB is a comparative nationwide cohort study using data from the French National Health Data System. The main inclusion criteria are: age ≥ 40 years, DT2 diagnosed for ≥ 7 years, with ≥ 2 additional cardiovascular risk factors plus a history of microvascular or macrovascular disease, except CAD. We estimated ≥ 90,000 eligible participants for our study. Data will be extracted from 01/01/2008 to 31/12/2019. Eligible participants will be identified during a first 7-year selection period (2008–2015). Each participant will be assigned either in experimental (CAD screening procedure during the selection period) or control group (no CAD screening) on 01/01/2015, and followed for 5 years. The primary endpoint is the incremental cost per life year saved over 5 years in CAD screening group *versus* no CAD screening. The main secondary endpoints are: total 5-year direct costs of each strategy; incidence of major cardiovascular (acute coronary syndrome, hospitalization for heart failure, coronary revascularization or all-cause death), cerebrovascular (hospitalization for transient ischemic attack, stroke, or carotid revascularization) and lower-limb events (peripheral artery disease, ischemic diabetic foot, lower-limb revascularization or amputation); and the budget impact for the French Insurance system to promote the cost-effective strategy. Analyses will be adjusted for a high-dimension propensity score taking into account known and unknown confounders. SCADIAB has been funded by the French Ministry of Health and the protocol has been approved by the French ethic authorities. Data management and analyses will start in the second half of 2021.

**Discussion:**

SCADIAB is a large and contemporary RWE study that will assess the economic and clinical impacts of routine CAD screening in T2DM people at a very high cardiovascular risk. It will also evaluate the clinical practice regarding CAD screening and help to make future recommendations and optimize the use of health care resources.

*Trial registration* ClinicalTrials.gov Identifier: NCT04534530 (https://clinicaltrials.gov/ct2/show/NCT04534530)

## Background

Type 2 Diabetes mellitus (T2DM) is a major public health problem, responsible for a wide range of clinical, economic and societal issues [1–4]. Despite the substantial improvement in cardiovascular prognosis observed in recent decades, cardiovascular disease, essentially coronary artery disease (CAD), remains the leading cause of death [5]. CAD is often severe and silent in patients with T2DM [6–10], which may encourage a systematic and broad screening in asymptomatic individuals. Previous randomized controlled trial (RCT) did not provide evidence that routine screening for silent CAD may reduce the incidence of major cardiovascular events and death in people with T2DM [11–15]. Only one previous study showed that screening for silent CAD, compared with no screening, was associated with a reduced risk of minor cardiovascular events in T2DM patients with at least 2 cardiovascular risk factors [16]. However, the results of this monocentric and small sized study have never been corroborated by subsequent RCTs, although larger, multicentric and testing hard and validated clinical outcomes (major cardiovascular events and all-cause death) (Table 1). The DIAD (Detection of Ischemia in Asymptomatic Diabetics) study showed a comparable 4.8-year incidence of major cardiovascular event (a composite of cardiovascular death or non-fatal myocardial infarction) in 1123 T2DM participants who experienced CAD screening compared with those who did not [11]. Similar findings were reported in further large multicenter RCTs and a meta-analysis [12–15]. Nevertheless, some uncertainties remain in terms of benefit of CAD screening strategy in T2DM patients at very high cardiovascular risk, particularly those with peripheral atherosclerosis, chronic kidney disease (CKD) or any microvascular disease.

**Table 1 Tab1:** Randomized controlled trials evaluating the effect of systematic screening of coronary artery disease in the risk of major cardiovascular adverse events in people with diabetes

Study	Population	Inclusion period	Follow-up (years)	Primary outcome	Sample size	Number of events	Expected incidence (%/year)	Observed incidence (%/year)	Hazard ratio (95% CI)
Faglia et al. [16]	T2DM Age 46–75 years +$$\ge $$ 2 CV risk factors	1998–1999	4.5	Major (cardiac death or MI) or minor (resting and effort angina) event	141	19	3	3	-
DIAD [11]	T2DM Age 50–70 years	2000–2002	4.8	Non-fatal MI or CV death	1123	32	1—2	0.6	0.88 (0.44–1.88)
DYNAMIT [12]	DT2M Age 55–75 years +$$\ge $$ 2 CV risk factors	2000–2003	3.5	All-cause death, non-fatal MI, non-fatal stroke, HH requiring hospitalization or visit to emergency department	631	54	5.5	2.4	1.00 (0.59–1.71)
FACTOR-64 [13]	T2DM + T1DM Men $$\ge $$ 50, Women $$\ge $$ 55 years diabetes duration $$\ge $$ 3 years or Men $$\ge $$ 40 years, Women $$\ge $$ 45y + Diabetes duration $$\ge $$ 5 years	2007–2013	4.0	All-cause death, nonfatal MI, or hospitalization for unstable angina	900	62	8	1.7	0.80 (0.49–1.32)
DADDY-D [14]	T2DM Age 50–70 years 10-year CV risk score ≥ 10%	2007–2012	3.6	Non-fatal MI or CV death	520	26	2.6	1.4	0.85 (0.39–1.83)

*T2DM* type 2 diabetes mellitus, *T1DM* type 1 diabetes mellitus, *CV* cardiovascular, *MI* myocardial infarction, *HH* heart failure

Despite this lack of evidence, most of guidelines recommend systematic screening for silent CAD in asymptomatic individuals with diabetes and high or very high cardiovascular risk [17–20]. Hence, a majority of physicians practice routine screening for silent CAD in patients with diabetes. We conducted a preliminary survey (unpublished data) in France in 2019 to determine the practices of 605 physicians in terms of screening for silent CAD in T2DM patients at a very high cardiovascular risk. A majority of participants (80% of cardiologists and 69% of diabetologists) reported a routine CAD screening practice with a sustained frequency: once a year (42%), once/2 years (20%), and once/3 years (33%).

A routine CAD screening induces high healthcare expenses as it leads to invasive investigations, endovascular and surgical revascularizations as well as intensification of pharmacological therapies. To the best of our knowledge, the cost-effectiveness of routine CAD screening has not been evaluated prospectively in population with T2DM and a very high cardiovascular risk. Only two economic studies, based on Markov models, have addressed this question by comparing different strategies in Japanese and American populations: no screening, screening (with stress echocardiography, myocardial scintigraphy coupled with stress test, or stress electrocardiogram) [21, 22]. Their results were very limited by model’s hypothesis; uncertainty surrounding epidemiological and utilities data used; and costs of care, which may differ greatly across countries. In this context of discrepancy between lack of evidence and current guidelines and clinical practice, we aim to estimate the effectiveness and cost-effectiveness of systematic CAD screening in patients with T2DM and a very high cardiovascular risk.

## Methods

### Study overview and design

The Cost-effectiveness of Screening of Coronary Artery disease in patients with type 2 DIABetes at a very high cardiovascular risk (SCADIAB) study is a retrospective and comparative real-world evidence (RWE) cohort study using data from the French National Health Data System (SNDS, *Système National des Données de Santé*), a claim database encompassing 98,8% of the whole French population [23].

### Study population

#### Inclusion criteria

Eligible participants must meet all of the following criteria:Age = 40 years or older,Affiliation to the general health insurance scheme in France,Diagnosis of T2DM,Duration of T2DM ≥ 7 years,Two or more additional cardiovascular risk factors (obesity, hypertension, hypercholesterolemia, or tobacco smoking using the chronic obstructive pulmonary disease (COPD) as a proxy),At least one microvascular or macrovascular disease: carotid stenosis, transient ischemic attack (TIA), stroke, lower-limb peripheral artery disease (PAD), CKD, severe diabetic retinopathy with requirement of laser photocoagulation, or peripheral or autonomic diabetic neuropathy.

Diagnosis will be determined based on the list of 100% health insurance coverage for chronic diseases in France (including T2DM, hypertension, TIA, stroke, PAD, CKD, COPD), the history of diseases of interest or surgery (coronary, carotid or lower-limb revascularization, bariatric surgery, kidney transplantation) according to the International Classification of Diseases Code Tenth Revision (ICD-10) (Additional file 1: Table S1), or at least 3 deliveries of one or more corresponding drugs as appropriate (antidiabetic, anti-obesity, antihypertensive or lipid-lowering drugs) over one year.

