#### Exclusion criteria

One of the following:The presence of CAD (defined as a history of acute coronary syndrome, coronary revascularization, angina pectoris, or unstable angina).Any visit to an emergency department for chest pain resulting for admission to a cardiac intensive care unit.

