### Study groups and methods of CAD screening

#### Screening group

Individuals who had at least one screening exam (stress electrocardiogram test, stress echocardiography, myocardial scintigraphy coupled with stress test or pharmacological stimulation using adenosine, or coronary CT scan) (Table 2) during the selection period (2008–2015).

**Table 2 Tab2:** Codes used to identify tests to screen coronary artery disease

Tests	Procedure codes
Stress test	DKRP004, EQRP002, EQRM001
Myocardial scintigraphy coupled with stress test or pharmacological stimulation using adenosine	DAQL001, DAQL010, DAQL011, DAQL009
Stress echocardiography	DAQM003, DZQM002, DBQM001
Coronary CT scan	ECQH010
Procedure codes: Codes of the French classification of medical procedure (CCAM)	

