#### No-screening group

Participants who never experienced a screening exam as described above during the selection period (2008–2015), except resting electrocardiogram.

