### Study endpoints

#### Primary endpoint

The incremental cost per life year saved over 5 years in CAD screening group *versus* no CAD screening.

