### Strengths and limitations

The key strength of our study is the collection of a comprehensive range of clinical features, cardiovascular procedures, history of pharmacological therapies or surgery, major events and survival status in the whole French population of patients with T2DM and a very high cardiovascular risk during an overall period of 12 years. SCADIAB findings will have a broader generalizability for all T2DM patients at a very high cardiovascular risk. Our study will provide a line of complementary evidence (further to RCTs’ findings) in terms of routine CAD screening in a contemporary cohort of patients with T2DM in real-world settings. SCADIAB will be more economical and time efficient than RCT, but a number of intrinsic limitations need to be acknowledged. The retrospective and non-randomized design of our study is subject to bias (selection, information, detection) and confounding factors. To limit selection bias, our study population will be rigorously defined using pre-specified inclusion criteria (T2DM for at least 7 years, with at least 2 cardiovascular risk factors and one or more organ damage) extracted from reliable and valid SNDS database. The 7-year selection period leading to assignment of each individual to one of the two study arms (CAD screening or absence of CAD screening) will limit information bias. We will use validated algorithms to identify inclusion criteria and endpoints [29–31]. Also, the cardiovascular investigation required for study arms assignment (stress test, scintigraphy, stress echocardiography…) will be recorded exhaustively in the SNDS database. We believe that the detection bias will be limited in our study as we have access to the SNDS database covering the whole French population including death registry. Finally, we will use the hdPS method to control measurable confounding factors as well as unknown or unmeasurable ones [32–34].

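### Eligibility is not restricted to plausible candidates for screening, so patients with limited life expectancy probably collect in the no-screening arm and tilt life years gained towards screening

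*Protocol article*

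**What the plan says.** All references are to the Protocol article.

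- **Inclusion criteria:** "Age = 40 years or older", with no upper bound, plus long-standing type 2 diabetes, at least two further cardiovascular risk factors and at least one vascular complication.
- **Exclusion criteria:** there are two. The first is "The presence of CAD (defined as a history of acute coronary syndrome, coronary revascularization, angina pectoris, or unstable angina". The second is "Any visit to an emergency department for chest pain resulting for admission to a cardiac intensive care unit". Nothing concerns life expectancy or suitability for a test.
- **Screening group:** "Individuals who had at least one screening exam" at any time in the selection period. The listed tests include "myocardial scintigraphy coupled with stress test or pharmacological stimulation using adenosine, or coronary CT scan".
- **No-screening group:** "Participants who never experienced a screening exam as described above during the selection period", apart from resting electrocardiograms. The reason for not being tested plays no part.
- **Primary endpoint:** "The incremental cost per life year saved over 5 years in CAD screening group" compared with no screening. All-cause death is also a component of the cardiac composite (Clinical endpoints).
- **Statistical analysis plan:** a propensity score from about 500 variables, reduced to 30 components, checked by plotting its distribution in each arm and by standardised differences. Comparisons are made with and without adjustment for it. No step is given for the case where the two distributions do not overlap.
- **Strengths and limitations:** selection bias and confounding are acknowledged. The stated protection begins: "To limit selection bias, our study population will be rigorously defined using pre-specified inclusion criteria".

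**The concern.** The study asks whether to screen. Patients who were not realistic candidates for a test cannot inform that question, yet nothing keeps them out, and if untested they become controls by default. A patient in palliative care, or with metastatic cancer or dementia, is less likely than others to have been sent for a coronary test and much more likely to die within 5 years. If such patients are tested less often, the control arm loses life years for reasons unrelated to screening, and a screening effect of zero still shows a gain.

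The imbalance goes straight into the denominator of the primary ratio. The cost numerator is affected too, through end-of-life spending and the early end of cost accrual; the article does not allow the net direction to be derived. A bootstrap interval reflects sampling error only. With some 90,000 patients it could be narrow around a biased value.

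The inclusion criteria cited as the safeguard against selection bias concern diabetes duration, risk factors and organ damage. None concerns candidacy for screening.

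**Working it through.** **The plan's own figure.** Sample size estimation gives 2.4 million people with type 2 diabetes free of coronary disease, 38% with two or more risk factors and more than 10% with vascular disease: 2,400,000 × 0.38 × 0.10 = 91,200. This reproduces the stated minimum of 90,000. It is a feasibility count and makes no allowance for non-candidates.

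**Assumed inputs.** The article gives no age distribution, frailty share, death rate or testing rate by frailty, so all of these are assumptions:
- background death hazard 0.04-0.06 per year;
- death hazard in patients with limited life expectancy 0.35-0.60 per year;
- share of such patients 3-10% of controls and 0.5-1% of the screened;
- true effect of screening: zero.

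**Step 1: life years over 5 years** at constant hazard h, LY = (1 − exp(−5h)) / h.

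| h per year | LY |
|---|---|
| 0.04 | 4.532 |
| 0.06 | 4.320 |
| 0.35 | 2.361 |
| 0.60 | 1.584 |

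**Step 2: spurious gain** = (control share − screened share) × (LY background − LY frail).
- Smallest corner: (0.03 − 0.01) × (4.320 − 2.361) = 0.02 × 1.959 = 0.039.
- Largest corner: (0.10 − 0.005) × (4.532 − 1.584) = 0.095 × 2.948 = 0.280.

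**Step 3: yardstick**, a true 20% reduction in the background hazard.
- From 0.04 to 0.032: 4.620 − 4.532 = 0.089 life years.
- From 0.06 to 0.048: 4.445 − 4.320 = 0.126 life years.

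The ratio of artefact to true benefit runs from 0.039 / 0.126 = 0.3 to 0.280 / 0.089 = 3.2.

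**Step 4: a second, separately specified model**, with milder frail hazards and testing rates in place of shares. Assumed: half of non-frail patients screened, background hazard 0.04, frail hazard 0.20 per year (LY = 3.161). With 10% of the cohort frail and 10% of the frail screened:
- overall screened share: 0.10 × 0.10 + 0.90 × 0.50 = 0.46;
- frail share of the screened: 0.01 / 0.46 = 0.022;
- frail share of controls: 0.09 / 0.54 = 0.167;
- spurious gain: (0.167 − 0.022) × (4.532 − 3.161) = 0.20 life years.

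Other cases of this model, in life years, at frail hazard 0.20:

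| Frail share of cohort | 0% of frail screened | 10% | 30% |
|---|---|---|---|
| 5% | 0.13 | 0.10 | 0.05 |
| 10% | 0.25 | 0.20 | 0.10 |
| 20% | 0.46 | 0.36 | 0.18 |

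At frail hazard 0.30 the same cases run from 0.07 to 0.65. If frail and non-frail patients are screened equally often, or the frail are removed, the spurious gain is 0.00. Whenever the frail are screened less often, it favours screening.

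**Step 5: what adjustment would have to do.** All these figures are before adjustment. In the largest case of Step 2, adjustment would have to remove 1 − 0.089 / 0.280 = 68% of the artefact merely to bring it down to the size of a true 20% benefit. The article gives nothing from which the fraction actually removed could be computed.

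**The case against.** **Testing is not ruled out for frail patients.** One test at any time in seven years puts a patient in the screening arm, so someone with dementia or cancer in 2015 may have been tested while fit. Pharmacological scintigraphy and coronary CT count, so inability to exercise is no bar. In the survey cited in the Background, 80% of cardiologists and 69% of diabetologists reported routine screening in very-high-risk patients. This stands. A reader might infer that such patients sit almost wholly among controls, or that overlap is structurally absent. The documents support neither; they support probable over-representation.

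**Adjustment is planned.** If cancer, dementia and palliative care can be coded for an exclusion, they can also enter the score, and the planned plots are the usual way to see non-overlap. This also stands: part of the bias may go. However, the score is described only as an adjustment, and where screened counterparts are scarce, adjustment extrapolates.

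**The size is assumed.** True, and it is a pre-adjustment size. It shows only that the artefact can be as large as the effect of interest.

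**The overlap rule belongs in an analysis plan that is not shown.** Its absence from an article is not a fault by itself. The point rests on the eligibility lists, which are protocol content and are given here; the overlap rule is part of the remedy.

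**No age ceiling is needed.** Four of the five trials in Table 1 stop at 70 or 75 years, and a reader might infer that the open upper age is the mistake. It is not: FACTOR-64 lists no ceiling, age is measured and can be adjusted for, and the study aims at a broader population than the trials covered.

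**Conclusion.** The point holds in moderate form. The two exclusions leave in patients with coded limited life expectancy, the control definition takes them in when untested, and the primary denominator counts their deaths. If they are tested less often, which is likely but not documented, the bias favours screening.

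Under the first set of assumptions the artefact before adjustment is about 0.04-0.28 life years, or 0.3 to 3.2 times a true 20% mortality benefit of 0.09-0.13. The residual after adjustment is unknown. A reader might go further and infer that the published result will falsely show life years saved; the documents do not support that, because the imbalance, the hazards and the success of the score are all unmeasured here. The change is worth making before analysis, since it bears on the primary result and costs little.

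**What to change.** 1. **Exclusion criteria:** add an exclusion for metastatic cancer, palliative care or dementia coded by the index date (1 January 2015), applied identically to both arms. ICD-10 and the chronic-disease coverage list are already used to define the cohort.
2. **Statistical analysis plan:** limit the adjusted primary comparison to the range of the propensity score represented in both arms, and report how many patients this removes from each arm.
3. **Optional:** repeat the primary analysis in patients aged 40-75 as a pre-specified sensitivity analysis. A ceiling in the main analysis is not needed.

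The cost is one eligibility line, a filter on claims codes and one further run. The cohort becomes slightly smaller, by a number that cannot be computed from the article, and the study draws no conclusion for the excluded patients.

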#### Exclusion criteria

One of the following:The presence of CAD (defined as a history of acute coronary syndrome, coronary revascularization, angina pectoris, or unstable angina).Any visit to an emergency department for chest pain resulting for admission to a cardiac intensive care unit.

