### Recruitment of participants and follow‑up

The data will be extracted from January 1, 2008 to December 31, 2019. A selection period will be defined by the 7 years (January 1, 2008 to December 31, 2014) preceding the index date. It will enable us to identify eligible patients and measure all the variables needed for the calculation of the high dimension propensity score (hdPS). Each participant will be assigned to one of the two study groups on the index date (January 1, 2015), and then followed up to December 31, 2019 (Fig. 1).

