### Screening for silent CAD and risk of major cardiovascular events

Previous RCTs demonstrated no clinical benefit associated with routine CAD screening in asymptomatic T2DM patients, but population with a high cardiovascular burden and any organ vascular damage has not been investigated [11–14]. Also, the observed incidence of outcomes was much lower than expected in published RCTs evaluating the interest of routine CAD screening in individuals with T2DM (Table 1). The conduction of a new prospective RCT will be too expensive, time-consuming with difficulties for recruiting asymptomatic participants with a very high cardiovascular risk. Indeed, the DYNAMIT (Do You Need to Assess Myocardial Ischemia in Type-2 diabetes) study was stopped prematurely due to difficulties in recruitment of participants and a low incidence of cardiovascular events [12]. DYNAMIT included only one-fifth (631/3000) of the originally planned enrolment to detect a 20% relative risk reduction (RRR) in the primary endpoint (a composite of all-cause death, non-fatal myocardial infarction, non-fatal stroke, or heart failure requiring hospitalization or visit to emergency department) in people with T2DM at a high cardiovascular risk (aged 55 to 75 years with at least 2 other cardiovascular risk factors). A recent meta-analysis estimated that a large number of participants would be needed to demonstrate a potential benefit of the systematic CAD screening strategy to reduce the incidence of major cardiovascular events [15]. The optimal sample size for 20% RRR of major cardiac events should be 29,763 participants (19,548 for all-cause death). Therefore, a retrospective RWE study seems to be an appropriate approach to evaluate the long-term cost-effectiveness of systematic CAD screening strategy in T2DM subjects at a very high cardiovascular risk without known history of CAD. Of note, among 3.7 million people with diabetes in France, we estimate that at least 90,000 individuals will be eligible for our study in the SNDS database.

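### The CAD exclusion does not cover known but silent, medically managed coronary disease, so surveillance tests in such patients would count as screening

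*Protocol article*

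**What the plan says.** Under Exclusion criteria, the first criterion is "The presence of CAD (defined as a history of acute coronary syndrome, coronary revascularization, angina pectoris, or unstable angina". The second is "Any visit to an emergency department for chest pain resulting for admission to a cardiac intensive care unit". No other exclusion is listed.

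Under Screening group, the exposed are "Individuals who had at least one screening exam" from a list of four test types during the selection period. Nothing is required about the reason for the test or about coronary status before it. The no-screening group must have had none of these tests in the same period.

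The Discussion gives the target population as "T2DM subjects at a very high cardiovascular risk without known history of CAD". The Abstract likewise admits macrovascular disease other than CAD.

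**The concern.** The target is defined by what is known about the patient; the exclusion is defined by how the disease showed itself. The two differ for one group: patients whose coronary disease has been diagnosed but is silent, has caused no infarction and has not been revascularized. The article recognises that this group exists, because its Discussion cites a trial in silent CAD in which one arm had medical treatment alone.

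The gap is not neutral between the groups. A patient followed for known coronary disease is likely to have a stress test or scintigraphy at some point in seven years, and one such test is enough to join the screening group. Three planned results are exposed:

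- **Primary ratio.** The patient's coronary-care costs and deaths enter the incremental cost per life year on the screening side.
- **Clinical endpoints.** Any excess of cardiac events is attributed to the screening strategy.
- **Screening frequency.** Patients under surveillance would tend to fall in the high-frequency subgroups of the frequency–survival analysis, and would raise the reported number of exams per person per year.

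**Working it through.** **1. The definition against the target.** Take a patient with chronic ischaemic heart disease documented before any test that the study counts, without angina, infarction or revascularization, and treated with drugs.

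| Rule | Does it remove this patient? |
|---|---|
| Acute coronary syndrome | No, none occurred |
| Coronary revascularization | No, none done |
| Angina pectoris or unstable angina | No, silent |
| Emergency visit for chest pain with cardiac intensive care | No, silent |
| Discussion: no known history of CAD | Yes, the disease is known |

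The patient is outside the stated target and inside the cohort. One listed test then assigns the patient to screening.

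**2. The plan's own count.** Sample size estimation gives 2.4 million people with T2DM free of CAD, 38% with at least two risk factors, and more than 10% with vascular disease:

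2,400,000 × 0.38 × 0.10 = 91,200,

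which agrees with the stated minimum of 90,000 (+1.3%).

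**3. Sensitivity of the comparison (every input assumed).** Let q be the share of the cohort with known silent CAD, s the share of the cohort in the screening group, and k the mortality ratio of these patients to the others. Suppose that all of them are tested and that screening has no true effect. They then make up q/s of the screening group and none of the controls, and the unadjusted risk ratio is

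1 + (q/s) × (k − 1).

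| q | s | q/s | Ratio, k = 1.5 | Ratio, k = 2.0 |
|---|---|---|---|---|
| 1% | 70% | 1.4% | 1.007 | 1.014 |
| 1% | 30% | 3.3% | 1.017 | 1.033 |
| 3% | 50% | 6.0% | 1.030 | 1.060 |
| 5% | 50% | 10.0% | 1.050 | 1.100 |
| 10% | 70% | 14.3% | 1.071 | 1.143 |
| 10% | 30% | 33.3% | 1.167 | 1.333 |

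Across this grid the distortion runs from about 1.01 to 1.33. For scale, the point hazard ratios reported in the article's Table 1 run from 0.80 to 1.00. The grid shows only that the effect could be negligible or material; it does not estimate it.

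**4. Cost in numbers.** Removing q = 1%, 3%, 5% or 10% of 91,200 takes out 912, 2,736, 4,560 or 9,120 patients and leaves 90,288, 88,464, 86,640 or 82,080.

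**The case against.** **The code list is not shown.** Diagnoses are identified through Additional file 1: Table S1, which may hold broader ischaemic heart disease codes. This stands as a limit. But the article itself states a closed definition, so if Table S1 is wider, the article misstates the rule and the two must be reconciled.

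**Old infarction.** A reader might infer that a patient with an infarction in 2006 slips through. The documents do not support that as a gap in the definition: an earlier infarction is a history of acute coronary syndrome, and the criterion sets no time limit. The article states "The data will be extracted from January 1, 2008 to December 31, 2019", but it does not say that earlier-dated diagnoses are ignored.

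**The coverage list.** A reader might take the list of long-term conditions, "including T2DM, hypertension, TIA, stroke, PAD, CKD, COPD", as proof that coronary coverage is not used. It opens as a list of examples and stands under the inclusion criteria, so silence there proves nothing.

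**Silent disease is common.** The Background says "CAD is often severe and silent in patients with T2DM". That is the rationale for screening. It does not say how many patients carry an existing diagnosis under drug treatment.

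**The study title.** The title promises patients with T2DM at very high cardiovascular risk, not a cohort free of CAD. The conflict is with the Discussion and the Abstract only.

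**Adjustment and direction.** The hdPS draws on about 500 variables and may absorb part of the imbalance, although the article calls the primary estimate gross and plans comparisons with and without adjustment. Adjustment also cannot turn a surveillance test into a screening test. The net direction of all biases is not settled: if the exclusion runs through the selection period, it could also remove screened patients revascularized after a positive test, which pushes the other way.

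**Deliberate restriction.** Excluding only manifest CAD avoids deleting disease that screening found. This is a fair reason for care with dates. It does not justify keeping disease that was known beforehand.

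**Conclusion.** The concern holds in a limited form. Followed as written, the plan keeps patients with known, silent, medically managed CAD and counts their surveillance tests as screening, contrary to its stated target. This follows from the text and needs no assumption about numbers.

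The consequence is a tendency, not a measured bias: against screening in the cost and outcome comparison, and upward in screening frequency. Its size cannot be derived from the documents. The range of 1.01 to 1.33 rests wholly on assumed prevalence, screening share, mortality ratio and complete testing, and it is before any adjustment. It should not be quoted as an expected error.

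**What to change.** In the Exclusion criteria, and consistently in Table S1, add chronic ischaemic heart disease diagnoses and long-term-disease coverage for coronary disease to the CAD definition.

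Apply the added items by a date that is the same for both groups and precedes exposure. Two options are:

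- disease recorded with an onset before the start of the selection period, where the coverage or diagnosis date allows it; or
- disease recorded in a fixed early baseline window, with tests counted towards exposure only after that window.

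A date tied to each patient's first exam should not drive the main exclusion. Controls have no such date, because the design has a single index date of 1 January 2015. Applying the added codes up to the index date would be worse, since it would remove CAD discovered by screening.

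As a sensitivity analysis, also drop screened patients whose CAD code precedes their first exam. This acts on one group only, so it is a check and not the main analysis.

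The cost is a few more codes and a slightly smaller cohort; the baseline-window option also gives up some exposure time. Even a 10% loss would leave about 82,000 patients, above the 29,763 that the Discussion cites for a 20% relative reduction in major cardiac events.
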